## Abstract

**Background:**

Type 2 diabetes is a major challenge for Canadian public health authorities, and regular physical activity is a key factor in the management of this disease. Given that less than half of people with type 2 diabetes in Canada are sufficiently active to meet the Canadian Diabetes Association's guidelines, effective programs targeting the adoption of regular physical activity are in demand for this population. Many researchers have argued that Web-based interventions targeting physical activity are a promising avenue for insufficiently active populations; however, it remains unclear if this type of intervention is effective among people with type 2 diabetes.

**Objective:**

This research project aims to evaluate the effectiveness of two Web-based interventions targeting the adoption of regular aerobic physical activity among insufficiently active adult Canadian Francophones with type 2 diabetes.

**Methods:**

A 3-arm, parallel randomized controlled trial with 2 experimental groups and 1 control group was conducted in the province of Quebec, Canada. A total of 234 participants were randomized at a 1:1:1 ratio to receive an 8-week, fully automated, computer-tailored, Web-based intervention (experimental group 1); an 8-week peer support (ie, Facebook group) Web-based intervention (experimental group 2); or no intervention (control group) during the study period.

**Results:**

The primary outcome of this study is self-reported physical activity level (total min/week of moderate-intensity aerobic physical activity). Secondary outcomes are attitude, social influence, self-efficacy, type of motivation, and intention. All outcomes are assessed at baseline and 3 and 9 months after baseline with a self-reported questionnaire filled directly on the study websites.

**Conclusions:**

By evaluating and comparing the effectiveness of 2 Web-based interventions characterized by different behavior change perspectives, findings of this study will contribute to advances in the field of physical activity promotion in adult populations with type 2 diabetes.

**Trial Registration:**

International Standard Randomized Controlled Trial Number (ISRCTN): ISRCTN15747108; http://www.isrctn.com/ISRCTN15747108 (Archived by WebCite at http://www.webcitation.org/6eJTi0m3r)

## Introduction

### Background

In 2009, 2.4 million Canadians were living with type 2 diabetes (T2D), and this number is expected to grow to 3.7 million by 2019 [1]. Scientific evidence increasingly shows the importance of regular moderate-intensity aerobic physical activity (PA) as a means of reducing the risk of complications associated with T2D [2-4]. Despite this body of evidence, self-reported measures suggest that only 30 to 40% of Canadians with T2D are meeting the Canadian Diabetes Association's guidelines [5,6]. Accordingly, innovative strategies aimed at promoting the adoption and maintenance of regular PA among Canadians with T2D are needed [1], and information technologies such as the Internet are a promising avenue for the development of large-scale interventions with behavior change purposes [7-11]. The evolution of Canadian Internet use also suggests that public health organizations should take advantage of this technology to develop and deliver services [12-14], including services targeting populations with chronic diseases [15] and adults ranging from 18 to 65 years of age [16-18].

To date, a significant number of scientific reviews have studied the effectiveness of Web-based interventions designed for PA adoption and/or maintenance, with evidence showing that they can be effective across various populations and settings [19-24]. However, only a few studies have attempted to develop Web-based PA-oriented interventions specifically for people with T2D, which have only produced mixed results so far [25-27]. Among these studies, the most successful interventions have been characterized by the following [25,27]: (1) they were theory-based; (2) they included goal-setting activities; (3) they included interactive tracking and personalized feedback components; and (4) they provided opportunities for peer support. In line with these insights, two web-based interventions using different behavior change perspectives will be evaluated and compared in this study regarding their effectiveness in promoting the adoption and maintenance of regular moderate-intensity aerobic PA in adults with T2D.

The first intervention consists of a fully automated, computer-tailored, Web-based intervention developed from the perspective of offering tracking and personalized feedback. In eHealth research, the technology underlying the tracking and personalized feedback component of interventions is known as “computer tailoring,” which can be defined as the generation of personalized feedback by a computer program based on prior individual assessment(s) [28]. This technology follows principles of face-to-face counselling and assesses individuals’ perceived health behavior status as well as the determinants that influence their motivation and behavior. Next, tailored feedback is provided about these determinants based on individuals’ answers and personal characteristics. According to the Elaboration Likelihood Model [29], the provision of tailored feedback will result in more thoughtful information processing via the central route of persuasion, since tailored messages are perceived as being personally relevant and thus encourage the person to pursue the desired behavior [30]. The technology of computer tailoring has proven to be more effective than more general types of health behavior change interventions, including those targeting PA adoption [7,31-33]. Yet, to our knowledge, only a few studies to date have used computer-tailoring technologies for the purpose of promoting regular moderate-intensity aerobic PA among adults with T2D [34-36].

The second intervention consists of a peer support, Web-based intervention that was developed from the perspective of offering Web-based opportunities for peer support. Within a health care context, peer support is defined as “the provision of emotional, appraisal, and informational assistance by a created social network member who possesses experiential knowledge of specific behavior or stressor and similar characteristics as the target population, to address a health-related issue of a potentially or actually stressed focal person” [37]. Social networking sites, of which Facebook is the most popular platform [38], can offer an innovative way of delivering peer support interventions to promote the adoption of health-related behaviors [39]. In this regard, the use of Facebook as a means of offering opportunities for peer support for promoting PA is relatively new. Evaluative studies published to date demonstrate the potential of this platform among young adult cancer survivors [40], healthy adults [41], female undergraduate students [42], female college freshmen [43], and government employees with metabolic syndrome [44]. Yet, to our knowledge, no study to date has used this platform for the purpose of enabling adults with T2D to share their experiences, concerns, and progress with their peers regarding the adoption of regular moderate-intensity aerobic PA specifically.

A substantial body of evidence stresses the importance of using a theoretical framework to inform the development of behavior change interventions [7,25,45]. The development of both interventions was thus based on the I-Change Model [46]. The I-Change Model is a theoretical framework that integrates the main concepts of several social cognitive theories (eg, Theory of Planned Behavior [47], Social Cognitive Theory [48], Health Belief Model [49], and the Transtheoretical Model [50]). The I-Change Model distinguishes 3 phases and their corresponding determinants in the behavior change process. For instance, to promote regular moderate-intensity aerobic PA in adults with T2D, an intervention should (1) increase a person’s awareness about the importance of practicing moderate-intensity aerobic PA; (2) motivate the person to practice moderate-intensity aerobic PA; and (3) transfer this motivation to the adoption of regular moderate-intensity aerobic PA [51]. Furthermore, the I-Change Model assumes that the determinants of the 3 phases mentioned above are affected by, among other influences, channel factors, which refer to the methods used to deliver messages. In this research project, the computer-tailoring component and peer support component are considered to be two different channels for message delivery. It is hypothesized that these channels will foster the adoption of regular moderate-intensity aerobic PA through cognitive changes (eg, attitude, social influence, self-efficacy, intention) [37,52].

In addition, to explore a current trend in Web-based interventions with health behavior change purposes [53-58], concepts derived from the Self-Determination Theory (SDT) [59] and Motivational Interviewing (MI) [60] are added to the I-Change Model as elements of the theoretical framework. SDT is a theory focusing on types of motivation rather than solely on the amount of motivation [59], while MI is a counseling approach using a collaborative style of communication to strengthen motivation and commitment to change in individuals [60]. As it has the potential to foster more autonomous motivation toward adopting and maintaining health behaviors in individuals [61], the integration and application of SDT and MI into behavior change interventions have been extensively discussed and encouraged in the PA domain in recent years [62-68]. Recent positive findings from a randomized controlled trial highlighted that more research on the effects of SDT and MI in Web-based PA behavior change interventions is needed [69].

### Aim of the Study and Hypotheses

The primary aim of this study is to evaluate the independent effectiveness of two Web-based interventions in promoting regular moderate-intensity aerobic PA among insufficiently active adult Canadian Francophones with T2D. In line with this aim, it is hypothesized that the Web-based computer-tailored intervention (H1) and the Web-based peer support intervention (H2) will be more effective at increasing moderate-intensity aerobic PA levels compared to a control group at 3 and 9 months after baseline. Another aim of this study is to compare the relative effectiveness of the two Web-based interventions at increasing moderate-intensity aerobic PA levels. Hence, the third hypothesis is that participants in both intervention groups will show a different level of moderate-intensity aerobic PA at 3 and 9 months after baseline. This hypothesis is formulated bilaterally, because no study to date has compared these two methods.

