### Randomization

Two websites were created for this study: one to host activities related to the computer-tailored intervention, and the other to host activities for the peer support intervention and those of the control group. Randomization with a 1:1:1 allocation ratio was performed in three steps. First, all Diabète Québec newsletter recipients with T2D who were between 18 and 65 years of age received invitation emails to participate in the study, resulting in 6425 potential participants. Next, 35% of these 6425 potential participants were randomly sampled by Diabète Québec via a computer algorithm to receive emails with a URL link redirecting them to the first website (computer tailoring group). Meanwhile, the remaining 65% of potential participants received emails giving them access to a URL redirecting them to the second website. Finally, potential participants who had been redirected to the second website were then allocated randomly by the web solution company responsible for the website development to either the peer support intervention group or the control group via a computer algorithm. The randomization procedures mentioned above were conducted independently of the research team. This is an open-label RCT, meaning that participants and investigators know who has received which intervention.

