### Statistical Analysis

Descriptive statistics will be used to summarize the baseline characteristics of the participants for sociodemographic variables (ie, origin, occupation, gender, age, and education), anthropometric variables (ie, height, weight, and body mass index), psychosocial variables (ie, attitude, social influence, self-efficacy, type of motivation, and intention), and PA level. In line with the hypotheses, linear mixed model analyses for repeated measures will be used to examine the effectiveness of the computer-tailored intervention (H1) and peer support intervention (H2) relative to the control group and also to compare both interventions to each other (H3). A linear mixed-model approach is very well suited for modelling data containing repeated measures from several participants [103] and has the advantage of providing better capabilities for handling missing observations when data are missing at random, compared to more traditional approaches such as repeated measures analysis of variance [104,105]. In accordance with the statistical procedure and for each analysis, group, time, and time × group will be included as independent variables and minutes per week of moderate-intensity aerobic PA will be included as the dependent variable. Analyses will be adjusted for sociodemographic characteristics and other relevant variables that significantly differ between the 3 study arms at baseline. In the presence of statistically significant interaction terms, post-hoc tests will be applied to compare differences between all pairs of means. All pairwise tests of the computer-tailored or peer support interventions compared to the control group will be 1-tailed, and tests comparing both interventions together will be 2-tailed. Finally, potential mediators of the interventions’ effects will be explored. Based on the theoretical framework (Figure 1), a mediation analysis will be conducted involving a multicategorical independent variable (both interventions relative to control group), with type of motivation and intention as mediator variables in serial, and PA behavior as the dependent variable. Hayes and Preacher’s SPSS macro will be used for exploring the potential mediators [106]. The statistical analyses will be conducted with SPSS 22.0.

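### H3 is worded as a difference in activity level at follow-up although the aim concerns increases in activity, so the planned pairwise tests, most naturally read, carry any baseline gap between the two interventions

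*Protocol article*

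**What the plan says.** Under Aim of the Study and Hypotheses, the second aim is to "compare the relative effectiveness of the two Web-based interventions at increasing moderate-intensity aerobic PA levels". H1 and H2 are likewise worded in terms of increasing activity. H3, presented as following from the second aim, is that "participants in both intervention groups will show a different level of moderate-intensity aerobic PA at 3 and 9 months after baseline".

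Under Statistical Analysis, weekly minutes of moderate-intensity activity is the dependent variable of a linear mixed model in which "group, time, and time × group will be included as independent variables". The decision step is: "In the presence of statistically significant interaction terms, post-hoc tests will be applied to compare differences between all pairs of means". For H3, "tests comparing both interventions together will be 2-tailed"; comparisons with control are one-tailed. The only provision for baseline differences is conditional: "Analyses will be adjusted for sociodemographic characteristics and other relevant variables that significantly differ between the 3 study arms at baseline".

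Under Randomization, "35% of these 6425 potential participants were randomly sampled by Diabète Québec via a computer algorithm to receive emails with a URL link" leading to the computer-tailored website. The remaining invitees were sent to a second website and randomized there between peer support and control. Under Eligibility and Recruitment, eligibility was self-reported on the websites during registration, that is, after the first split.

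**The concern.** Effectiveness at increasing activity is a statement about change. A different level at follow-up is not: two arms that start apart and rise by the same amount satisfy H3 as worded while being equally effective.

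The interaction test does concern change, but it serves only as a gate, and it covers all three arms. If both interventions beat control equally, the gate tends to open although they do not differ from each other. If the pairwise test that follows compares levels, a pre-existing gap can be reported as a difference in effectiveness, or an opposite gap can hide a real one. The Discussion wants the trial to show which of the two behavior change perspectives should come first, and that conclusion rests on H3.

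A systematic gap is conceivable because self-selection and the eligibility check came after invitees had been split between two websites, which differed in design apart from the home page. This bears on H3 and H1, whose arms enrolled through different sites. H2 compares arms randomized within one site.

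**Working it through.** **1. The article's own figure.** The sample size section gives N = 204 for a 3 × 3 mixed design, alpha .05, power .80 and d = .20. Take the within-between interaction, read d = .20 as f = d/2 = 0.10, and assume a visit correlation ρ = .5 (not stated):

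λ = N·m·f²/(1−ρ) = 204 × 3 × 0.01/0.5 = 12.24, with df = (3−1)(3−1) = 4 and (204−3)(3−1) = 402. Power is 0.806.

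The figure is reproduced exactly, so the sizing fits a test of differential change.

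**2. What each contrast estimates.** Let two equally effective interventions differ by g at baseline, with a fraction p of the gap remaining at follow-up (SD 1 at each visit):

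- level contrast: p·g
- change contrast: p·g − g
- follow-up adjusted for baseline: p·g − ρ·g

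With g = 0.2 and ρ = .5:

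| Gap remaining | Level | Change | Baseline-adjusted |
|---|---|---|---|
| all (p = 1) | 0.2 | 0 | 0.1 |
| half (p = .5) | 0.1 | −0.1 | 0 |

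**3. One level test, no gate.** With 234/3 = 78 per arm, the noncentrality is g·√(78/2). For g = 0.2 it is 0.2 × 6.245 = 1.25, giving about 24% rejection. For g = 0.3 it is 1.87, giving about 47%. For g = 0 the rate is 5%.

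**4. The planned sequence, simulated.** Assumptions: 78 per arm, SD 1, equal correlation .5, complete data and a fully persistent gap. The interaction F test (4 df) at .05 is the gate, followed by two-sided .05 tests of the two interventions at 3 and 9 months (3000 runs per setting). The table gives the chance of a false H3 claim at either visit when both interventions have the same effect. Ranges are across separate runs.

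| Effect of both against control | Gap 0, level | Gap 0.2, level | Gap 0.3, level | Change contrast after the gate |
|---|---|---|---|---|
| none | 1% | 3% | 4% | 3% |
| 0.2 SD | 3% | 9–10% | 14–15% | 5% |
| 0.4 SD | 7–9% | 27–29% | 47–48% | 9% |

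The change column does not depend on the gap when the gap persists fully. At a correlation of .62 (the one-month test-retest value quoted for the activity questionnaire) and a 0.4 SD effect, the level rates are 31% and 53%. With 47 per arm (0.60 × 78 = 46.8, the assumed completion rate) and a 0.4 SD effect, they are about 15% and 25%.

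**5. Does the conditional adjustment catch it?** A three-arm baseline test flags a 0.2 SD gap in about 24% of trials and a 0.3 SD gap in about 48%. With a 0.4 SD effect, about 19% to 23% of trials declare a false H3 difference with no baseline flag.

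**6. If the gap fades.** With a 0.2 SD gap of which half persists, and a 0.4 SD effect, the gated false-claim rates are about 11% for level, 15% for change and 8% for baseline-adjusted. This agrees with step 2: here the change contrast overcorrects.

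**7. Precision.** Relative variances are 1 for level, 2(1−ρ) for change and 1−ρ² for baseline-adjusted. At ρ = .5 these are 1, 1 and 0.75. Below .5 the change contrast is less precise than the level contrast.

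**The case against.** The strongest reply has four parts.

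- **Validity under randomization.** A follow-up level comparison is unbiased there, and a chance baseline gap is already covered by alpha. This stands. With no systematic gap the gated level test gives 7–9% over two visits, no worse than the change test. A reader might infer that any baseline imbalance makes H3 misleading, or that the arms did differ at baseline. The documents support neither: the 35% split was random, one activity ceiling applied to everyone, and no baseline data are given.
- **The cells are not named.** The text says only that "post-hoc tests will be applied to compare differences between all pairs of means", and an article may leave exact contrasts to a fuller plan. The model contains the change contrast and the sizing fits it. So it cannot be said that levels will certainly be tested. Still, the level reading is the one that matches H3's own wording.
- **The larger rates rest on favorable assumptions.** They need a 0.4 SD effect and a fully persistent gap, whereas the sizing uses d = .20. This stands. At 0.2 SD the rates are far lower, and with no effect the gate holds them to about 4% or less.
- **Changing the contrast is not a cure.** It overcorrects when a gap fades, and enrollment through different websites could also affect change itself. This stands and shapes the remedy.

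A reader might also extend the point to H2. Its two arms were randomized within the same website, so the selection argument does not reach it.

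**Conclusion.** The mismatch between the aim and H3 is in the text, and the planned decision step does not resolve it. The gate can open through an effect against control alone, and the level contrast that naturally follows carries any baseline gap between the interventions. This does harm only if the gap is systematic. The allocation of the computer-tailored arm before registration makes such a gap possible for H3 and H1 but does not demonstrate one.

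With 78 per arm, correlation .5 and a fully persistent 0.2 to 0.3 SD gap, false H3 claims at either visit are about 10–14% for a 0.2 SD effect against control and 27–47% for 0.4 SD. They are lower if the gap fades. The gap, effect, SD scale and correlation are all assumptions, because the article gives none of them for this outcome. No error rate was computed for H1. The point merits correction because the remedy is cheap and H3 is meant to guide a choice between approaches; it does not show that the trial's comparison is invalid.

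**What to change.** Restate H3 as a difference between the two interventions in change in activity from baseline to 3 months and from baseline to 9 months. In the analysis section, decide H3 and H1 with the matching time × group contrast from the planned mixed model: the arm difference at 3 or 9 months minus the arm difference at baseline. Alongside it, report an analysis of the follow-up values adjusted for baseline activity in all cases, not only when baseline differs significantly. Present follow-up levels as descriptive.

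Both analyses are needed because they fail in different directions. The change contrast is right if a gap persists fully and overcorrects if it fades. The baseline-adjusted analysis removes only part of a fully persistent gap. If they disagree, the report should say so. Neither fully cures selection by website.

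The cost is one sentence in the hypotheses, one or two in the analysis section, and contrast statements in a model already planned. No new data and no change in sample size are needed. The statistical price is lower precision of the change contrast if the visit correlation is below .5. Because the article says that data analysis is under way, the clarification should be dated and disclosed in the report.
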